### Interventions

Interventions in both arms of the study will be delivered by therapists working in the CAMHS teams taking part in the study. As part of study set up, all therapists taking part in the study will be randomly selected to either deliver MBT or treatment as usual. Therapists will be stratified by NHS banding, which takes into consideration profession and level of experience, to ensure that any systematic differences between groups are due to the model of intervention. Therapists who have had previous training in MBT will by default be allocated to the MBT arm of the study.

#### MBT

The adaptation of MBT used in this study is a manualized, transdiagnostic model designed for children aged 6–12 and their carers. It aims to promote adaptive ER by attending to the capacity to understand oneself and others in terms of underlying mental states. MBT consists of 6–8 sessions, delivered fortnightly, which can flexibly involve different members of the family, with a primary focus on promoting mentalizing and emotion regulation in the parent-child relationship (see Fig 3). Therapists randomly allocated to deliver treatment for the intervention group will receive a 3-day MBT training, plus fortnightly group supervision to support treatment fidelity. Practitioners are supported by an interactive online treatment manual and the use of a self-completed MBT Fidelity Scale (https://manuals.annafreud.org/mbt-c/index.html).

**Fig 3 pone.0289503.g003:**
[figure not shown]
MBT logic model.

#### Treatment as Usual (TAU)

The control group will be offered TAU. As there is no single evidence-based treatment for this group, and because practice is not standardised across CAMH services in England, TAU is likely to include CBT, parenting groups, and/or children’s social skills groups. Scoping work with CAMH services has confirmed that 6–8 fortnightly sessions would be the usual length of intervention for this client group. Therapists will be provided with usual supervision, in line with existing practice in participating CAMHS teams. As part of the study, more detailed data about TAU will be collected, including type of intervention, treatment intensity and professionals offering treatment.

### Discontinuation and withdrawal

Children and families can withdraw from either treatment or the trial without further explanation at any point. Where children or families withdraw from treatment, they will be invited to continue to participate in the trial. Reasons for discontinuing or withdrawal from the trial will be recorded, where families agree to provide such a reason. If a child requires more intensive care, such as inpatient hospitalization, the participant can be exited from the treatment, if this is clinically indicated, but will be encouraged to remain part of the study.

### Data collection

There will be three types of data collected: questionnaires, online tasks (subject to testing of feasibility during the internal pilot phase) and a semi-structured interview.

Questionnaire data will be collected using a secure, browser-based web application for developing, maintaining, and managing different types of surveys and securing online/offline data collection (REDCap). Participants will have the option to self-complete these questionnaires by following a link to the REDCap webpage, or to complete them via video or telephone call with a member of the research team. If collected during the video call, the responses to questionnaires will not be video recorded. One questionnaire (Service Use Record) will be completed by the participant’s local CAMHS team.

#### There are two tasks

A parent-child interaction task, and a child task (the Test of Emotional Comprehension; TEC). These interactive tasks will take place during a video call between the family and a member of the research team and part of the video call will be recorded. The child’s responses to the questions in the TEC task will be collected in real-time during the video call and entered directly into REDCap by the member of the research team conducting the call. The parent-child interaction task is facilitated by the member of the research team and the video call recorded; the recording is saved securely and later analysed and scored. All data entered directly into REDCap is securely stored with UCL’s Data Safe Haven.

The semi-structured interviews are part of the implementation and process evaluation (see Outcome Measures). They will take place after treatment has ended during an online call and audio recorded by the research team. The recording will be saved securely at on Anna Freud Centre (AFC) secure servers and transcribed and analysed.

For families who do not have access to the technology needed to facilitate a video call, data collection will take place over a telephone call, or else families will be given the opportunity to access the necessary technology at the CAMHS where treatment is taking place. In order to ensure that recruitment is inclusive, interpreters will be made use of to support data collection, where required.

The use of REDCap automatically scores and transmits the data, reducing the risk of data entry error. All research assistants are trained on the administering of the outcome measures. A summary of data collection timepoints is provided in the schedule of enrolment, interventions, and assessments (SPIRIT schedule) (Fig 1).

Participants’ personal data will be securely stored and only accessible by members of the ERiC research team at AFC. At the end of the study, data will be archived in a safe and secure location.

### Blinding

Parent/carers and children in the trial will not be blinded to intervention group. However, research assistants and those involved in data collection and analysis (including coding of ER tasks) will be blind to intervention group. Trial Managers will initiate the randomisation of participants and the outcome of the randomisation will be sent directly to staff at the CAMHS sites (see section ‘Randomisation’).

### Outcome measures

Brief, well-validated tasks and questionnaires will be administered at four points: baseline, 8 weeks after start of treatment (mid-treatment), 16 weeks after start of treatment (end of treatment) and 40 weeks after start of treatment (follow-up). An overview of all assessment points and outcomes are detailed in the SPIRIT (Fig 1).

In order to maximize clinical validity, data will be gathered through multiple methods (including questionnaire, interview and observational assessments) and from multiple perspectives (including self- and carer-reports). A consensus-based standard set of international measures [41] has been used. All questionnaire measures selected have established reliability, validity, utility/practicability and acceptability for this age group; they have also been reviewed by our parent co-applicants to ensure that they are acceptable, relevant and culturally appropriate. The pilot phase of the study will be used to test the feasibility of online, task-based assessment of parent-child ER capacity and mentalizing.

Primary outcome measure: Parent-rated Strengths and Difficulties Questionnaire (SDQ) Total Difficulties Score [42]. The SDQ is one of the most widely used mental health measures for children in the UK, covering both emotional (anxiety and depression) and behavioural (ADHD and conduct) symptoms.

Secondary outcome measures will include a range of carer- and child-report assessments and tasks to assess:

Emotional and behavioural problems,
Me and My Feelings [43, 44], a brief 16-item self-report measure for children, including both emotional and behavioural sub-scales.Personalized treatment goals,
Goal Based Outcomes (parent/carer-defined) [45], a personalized goal-based measure completed by parent/carers.Parenting stress,
Parental Stress Index–Short Form [46, 47], a 36-item parent/carer-report measure of stress and the parent-child relationship.Parental mentalizing capacity,
Parental Reflective Functioning Questionnaire [48], an 18-item parent/carer-report measure of parental mentalizing.Service use and costs.
Child and Adolescent Service Use Schedule (CA-SUS) [49], a questionnaire which records service use 3 months prior to baseline, during the course of the treatment, and between end of treatment and follow-upService Use Record, a questionnaire completed by CAMHS team to record the services offered and attended between baseline and end of treatment, and end of treatment and follow up.Emotion regulation in child and parent will be assessed using the following:

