**Materials and methods:**

Children referred to CAMHS aged 6–12 with mixed mental health problems (emotional and behavioural) as primary problem can take part with their parent/carers. Children will be randomly allocated to receive either MBT or treatment as usual (TAU) within the CAMHS clinic they have been referred to. MBT will be 6–8 sessions offered fortnightly and can flexibly include different family members. TAU is likely to include CBT, parenting groups, and/or children’s social skills groups. Parent/carers and children will be asked to complete outcome assessments (questionnaires and tasks) online at the start of treatment, mid treatment (8 weeks), end of treatment (16 weeks) and at follow up (40 weeks).

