### Randomization

Once mandatory elements of baseline data collection have been completed, participants will be randomized to either MBT or TAU, stratified by CAMH service and age group (6–9 years and 10–12 years old), using permuted blocks of size 2 within each stratum. The randomization sequence will be generated from random numbers generated in the R software for statistical computing [40] and pre-loaded into the REDCap data management platform, which will be used for data collection.

The randomization sequence will be stored but concealed within the REDCap data capture system. When all information relevant for stratification (CAMH service and age) has been completed, a researcher has the option to initialize randomization. Only then will the allocation be revealed within the REDCap database, and the CAMH service will be informed of the result of the randomization, so that treatment can be initiated.

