### Statistical data analysis plan for the main trial

The primary analysis aims to establish the difference between the MBT and TAU groups in the SDQ Total Difficulties score at the end of treatment (16 weeks, Hypothesis 1). Children are clustered within therapists, who in turn are clustered within CAMH services. The primary analysis model is a linear mixed effects model, with random intercepts for therapists and services, controlling for SDQ and age group at baseline. The evidence for a difference in SDQ scores after treatment will be assessed via a two-sided t-test of the coefficient of the treatment indicator variable, using a parametric bootstrap to estimate standard errors. A 5% significance level will be used as a cut-off to support a finding of superiority of MBT over TAU.

Analogous models will be used to assess the evidence regarding a difference between the MBT and TAU groups with respect to secondary outcomes (Hypothesis 2).

To investigate potential mediation of the effect of MBT on child mental health via improvement in emotion regulation (Hypothesis 3), we will conduct a mediation analysis using treatment allocation as the exposure, the Emotion Awareness Questionnaire (EAQ) score as the mediator, and the SDQ Total Difficulties Score as the outcome. We will additionally adjust for both EAQ and SDQ scores at baseline. Summary scores from the validated scales will be used, rather than latent variable scores, in order to maintain consistency with the effect estimates of the primary analysis. We will conduct an analogous mediation analysis using parental emotion regulation, assessed by the Difficulties in Emotion Regulation Scale (DERS). More complex mediation models will be developed using exploratory analyses.

To examine whether the improvement in child SDQ Total Difficulties is clinically significant at the individual level, the reliable change index [62] will be calculated for each participant using the SDQ scores at baseline and post-intervention. Children will be classified as recovered, improved, unchanged, or deteriorated. We will compare the distribution of this classification in the MBT and TAU groups using an ordinal logistic regression model.

We will also estimate the difference in treatment effect between MBT and TAU on SDQ Total Difficulties and all secondary outcomes at 40-week follow-up, using statistical models analogous to those for the primary analysis.

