All primary and secondary analyses will be carried out as intention-to-treat analyses. If some values at the primary endpoint are missing, the following strategy will be employed: 1) Evaluate likely processes of missingness and assess their potential for causing bias; 2) Conduct a complete cases analysis as the primary analysis; (3) Conduct information-anchored sensitivity analyses using controlled multiple imputation under MNAR assumptions to gauge the sensitivity of the trial results to potential violations in the MAR/MCAR assumptions [63, 64].

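### The 16- and 40-week assessments are timed from start of treatment, so time since randomisation can differ by arm and a child who never starts has no assessment date

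*Protocol article*

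**What the plan says.** The Outcome measures section counts the 8-week assessment and the two later ones from the same event: "16 weeks after start of treatment (end of treatment) and 40 weeks after start of treatment (follow-up".

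The Randomization section gives the order of events. Baseline comes first: "Once mandatory elements of baseline data collection have been completed, participants will be randomized to either MBT or TAU". Treatment comes after allocation: "the CAMH service will be informed of the result of the randomization, so that treatment can be initiated". The Abstract words the schedule differently and puts the first assessment "online at the start of treatment, mid treatment (8 weeks), end of treatment (16 weeks) and at follow up (40 weeks".

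The statistical data analysis plan takes the primary comparison on the "SDQ Total Difficulties score at the end of treatment (16 weeks, Hypothesis 1", adjusted for baseline SDQ and age group, with random intercepts for therapist and service. It states that "All primary and secondary analyses will be carried out as intention-to-treat analyses". If primary-endpoint values are missing, the complete-case analysis is primary and controlled multiple imputation under MNAR is a sensitivity analysis.

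The Interventions section has each therapist deliver either MBT or TAU. The Discontinuation and withdrawal section invites families who leave treatment to stay in the trial. The visible text sets no maximum wait between randomisation and first session, and no assessment date for a child who never has one.

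**The concern.** Start of treatment happens after randomisation and can be influenced by the allocation. Randomisation makes the arms comparable at randomisation, not at a later event whose timing may depend on the arm.

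Two consequences follow from the rule as written.

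- **Unequal elapsed time.** If one arm waits longer on average, its primary SDQ is taken later relative to baseline and randomisation. Any change in SDQ that comes with time alone then enters the treatment difference. If scores improve over time, the later-measured arm looks better.
- **Non-starters.** A child who never starts has no 8-, 16- or 40-week date. With complete cases as the primary analysis, such children may be lost, and not necessarily at the same rate in each arm.

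The economic evaluation has a related inconsistency. Under Outcome measures, the CA-SUS covers the treatment period and then the time from its end to follow-up. Under Economic evaluation, it covers everything since the previous assessment, which includes the wait. On the second reading, the costing period lengthens with the wait and may differ by arm.

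**Working it through.** **1. Time from baseline to primary endpoint**

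Let W be the time from randomisation to start of treatment.

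- Baseline is completed before randomisation (Randomization).
- Start of treatment is W weeks after randomisation, with W not bounded in the text.
- The primary SDQ is 16 weeks after start (Outcome measures).
- Randomisation to primary SDQ is therefore W + 16 weeks. Baseline to primary SDQ is that plus the short baseline-to-randomisation gap.
- For a child who never starts, W is undefined, and so is the date.

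**2. Can W differ by arm?**

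Therapists are specific to one arm (Interventions). About 40 therapists are expected (Sample size and power calculation), and the two trusts run 12 services (Study setting). If all 12 take part, that is 40/12 = 3.3 therapists per service, or about 1.7 per arm, so one full caseload could delay one arm only. Blocks of 2 within service and age group balance numbers, not time to start. Unequal waits are thus possible. The article does not report them.

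**3. The plan's own power figure**

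Inputs: N = 320, 160 per arm, 15% loss, difference 1.5, SD 5.0, correlation 0.6, therapist ICC 0.02, 8 children per therapist, two-sided 5%.

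- Analysed per arm: 160 × 0.85 = 136. Per therapist: 8 × 0.85 = 6.8.
- Design effect: 1 + (6.8 − 1) × 0.02 = 1.116.
- Variance: 25 × (1.116 − 0.36) = 18.9, which gives power of 81.2%, against 80.8% stated. The figure reproduces.
- A variant with variance 25 × 0.64 × 1.116 gives 83.3%, with standard error 5 × √(0.64 × 1.116) × √(2/136) = 0.51 points.

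None of these inputs depends on the assessment anchor, so changing it leaves N and power as they are.

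**4. Size of a timing imbalance (illustration)**

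Shift in arm difference = change in SDQ per week irrespective of arm × difference in mean wait. Both factors are assumptions; the documents give neither.

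| Change per week | 2 weeks | 4 weeks | 8 weeks |
|---|---|---|---|
| 0.02 | 0.04 (2.7%) | 0.08 (5.3%) | 0.16 (10.7%) |
| 0.05 | 0.10 (6.7%) | 0.20 (13.3%) | 0.40 (26.7%) |
| 0.10 | 0.20 (13.3%) | 0.40 (26.7%) | 0.80 (53.3%) |

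Entries are SDQ points, with the percentage of the 1.5-point target in brackets.

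Effect on the two-sided 5% test, with standard error 0.51:

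| Shift | Rejection rate if no true effect | Power for 1.5 if the shift works against MBT |
|---|---|---|
| 0 | 5% | 83.3% |
| 0.2 | 6.8% | 71.8% |
| 0.4 | 12.2% | 57.4% |
| 0.8 | 34.5% | 27.6% |

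With equal waits the shift is zero.

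**5. Room in the schedule**

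Eight fortnightly sessions run 7 × 2 = 14 weeks from first to last. Counting 16 weeks from randomisation with no allowance leaves 16 − 14 = 2 weeks for the wait before the visit precedes the end of an eight-session course.

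**The case against.** The strongest reply is that nothing shows the waits to be unequal. Children are randomised within service in blocks of 2, both arms are delivered by the same CAMHS teams with therapists allocated within NHS banding (apart from those already MBT-trained), and both arms are expected to run 6 to 8 fortnightly sessions. This stands: unequal waits are a possibility that the design leaves open, not a documented fact. A reader might also infer that TAU groups have fixed start dates. The article mentions groups but says nothing about when they start.

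A reader might work out a bias larger than the target: 0.3 points per week times six weeks is 1.8 points. That multiplies two assumed extremes. At 0.3 per week, scores would fall by 4.8 points in 16 weeks, about one SD (5.0), and by 12 points in 40 weeks, about half the presenting mean of 24.6. Regression to the mean after selection on a high score is also largely a remeasurement effect common to both arms, not a steady weekly fall. The documents do not support a figure of that size.

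A reader might further infer that the intention-to-treat statement is contradicted, or that non-starters are excluded. Neither is stated. Intention to treat concerns analysing children as allocated; families who leave treatment are invited to stay; and the therapist intercept is compatible with the assigned therapist. Losing non-starters is a risk created by the dating rule. The full protocol and the schedule figure are not visible and may hold a date for them, but the anchor itself is explicit text.

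Finally, the treatment-start anchor fits a question about outcome at end of treatment, and moving to randomisation has a price: with unequal waits, the slower arm would be measured with less treatment delivered. Recruitment began in April 2023 and pilot children count in the main analysis, so a full change would mix two endpoint timings. This stands, and it is why the fix distinguishes children already enrolled from those still to come.

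The Abstract's placing of the first assessment is an editorial slip, settled by the Randomization section.

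**Conclusion.** The point holds in a limited form. By the article's own text, the primary and follow-up assessments hang on a post-randomisation event with no bound on the wait before it, and a child who never starts has no date to be assessed on. This leaves the primary comparison open to a timing imbalance between arms and to loss of non-starters from the complete-case analysis.

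The size is not known. Under the assumed 0.02 to 0.10 points per week and a 2 to 8 week difference in mean wait, the shift is 0.04 to 0.80 points, or 3% to 53% of the 1.5-point target. It is zero if waits are equal. Any loss of non-starters would be additional and cannot be quantified from the article. The documents do not show that the trial is biased; they show that its stated timing rule does not prevent this bias.

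**What to change.** - **Dates.** Give every child assessment dates that do not depend on starting treatment. For children not yet enrolled, preferably count from randomisation plus one fixed allowance, identical in both arms, so that the 16-week visit still falls at about the end of treatment. If the treatment-start anchor is kept, assess children who have not started on a fixed date counted from randomisation.
- **Cluster.** Use the therapist assigned at allocation for the random intercept, so that non-starters have one.
- **Record and report.** For all children, including those already enrolled, record the dates of randomisation, treatment start and each SDQ. Report the wait by arm.
- **Sensitivity analysis.** Pre-specify an analysis of the primary outcome that accounts for weeks from randomisation to SDQ.
- **Costs.** Reconcile the CA-SUS period under Outcome measures with that under Economic evaluation, and report costs with the length of the period covered, by arm.
- **Abstract.** Correct the placing of the first assessment so that it agrees with the Randomization section.

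The cost is an amendment to the assessment schedule and its REDCap set-up. The drawback is that some children may still have sessions left at the 16-week visit. If the anchor changes during recruitment, two endpoint timings must be described and handled in the analysis. The sample size of 320 and the stated power are unaffected.

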### Monitoring of potential harm

To date there is a lack of agreement on suitable approaches to assessing and monitoring potential harm in the context of clinical trials for psychological treatments [57], especially in the context of child and family treatments. For the purposes of this study, we will adopt a broad definition of a Serious Adverse Event (sa). These include (in child or carer):

Violent behaviour resulting in serious physical harm to another personFamily relationship breakdownNew or escalated self-harmNew or escalated suicidal ideation (a preoccupation with suicide/thoughts about suicide, with no clear plans to take own life)Suicidal intent (concrete and deliberate plans to end own life, with a conscious desire to escape from the world and a resolve to act purposively in this regard, e.g., a suicide attempt. This may be a deliberate action or disclosing of a deliberate action)Other life-threatening eventsHospitalization due to drugs or alcohol, self-harm, or for psychiatric reasons (including, in-patient hospitalization, or significant disability/incapacity)Death, including suicide

SAEs may occur during the course of being involved in the trial. This could be irrespective of intervention or data collection or may be related to the intervention or data collection. Ascertaining a relationship between an SAE and the intervention in the trial must be assessed on a case-by-case basis. The individual identifying the SAE will therefore complete an SAE form, which contains an assessment of relatedness. Any SAEs considered to be ‘likely related’ to the intervention will be reviewed with clinical leads in the CAMHS team where the SAE has been identified and will qualify for expedited reporting to the ERiC Trial Steering Committee (TSC), who are responsible for monitoring the study. SAEs which are both related and unexpected will also be reported to the Research Ethics Committee (REC). Expected occurrences in the trial include the potential for some distress for participants as part of exploring painful experiences as part of therapy. For further information on SAEs, please refer the ERiC SAE procedure document.

